**Fig. 4 Fig4:**
[figure not shown]
Example of AWARE feedback form

**Table 2 Tab2:** Description of session handouts

Session	Input	Output
1	HIV knowledge quiz Number of sex partners in past 3 months and number of drinks before last sexual event, and perceptions of these behaviors by peers of same age and gender	Participant’s response for each item and the correct answer Normative feedback on number of sex partners and drinking before sex, based on data from a probability sample of young adults in Los Angeles experiencing homelessness
2	Triggers for unprotected sex Sex protective strategies Motivation to change rulers	List of people, situations, and feelings that are their personal triggers for engaging in unprotected sex How often they use each strategy Separate motivation rulers showing their level of motivation to practice safe sex and confidence that they can practice safe sex
3	Participant’s past month frequency and quantity of alcohol use, and perceptions of these behaviors by peers of same age and gender Decisional balance for substance use Motivation to change rulers	Normative feedback on frequency and quantity of alcohol use, based on data from the National Survey on Drug Use and Health (NSDUH) List of personal pros and cons of AOD use, with prompts to think about (a) how to get “pros” without AOD use; and (b) how to prevent “cons” from happening Separate motivation rulers showing their level of motivation to change their AOD use and confidence that they can change their AOD use
4	Alcohol consequences survey Drinking protective strategies	Which consequences the participant has experienced recently from drinking How often they use each strategy

### Analytic plan

Baseline data will be collected from participants using self-administered paper–pencil surveys, with the survey response forms then scanned and checked for accuracy. Follow-up data will primarily be collected using either scannable paper–pencil surveys or a web-based version of the survey. Participants who cannot complete a follow-up survey in one of these ways will be offered the option of completing the survey by phone (we expect these cases to be rare). Preliminary analyses will be conducted to: (a) examine the distribution of items and correct where necessary using, for example, a log transformation for skewed outcomes and/or centering of items as appropriate; and (b) determine whether the intervention and control groups differ on baseline characteristics (t-tests and Chi square tests). Observed differences at *p* < 0.20 may be subsequently controlled for in analyses testing intervention effects. All analyses will be intention to treat–that is, we will analyze people in the groups to which they were assigned, regardless of their attendance at the sessions. In terms of missing data and attrition, our general modeling approach will allow for the inclusion of all study participants who completed the baseline survey. We will explore patterns of missingness and use logistic regression models to gain a better understanding of the baseline predictors of study drop out (i.e., non-completion of the 3-, 6-, and 12-month assessments). To accommodate missingness in analyses we will use either an inverse probability weighting approach or multiple imputation [81].

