**Methods/design:**

In a cluster-cross-over randomized controlled trial, 18–25 year olds will receive the AWARE risk reduction program (n = 200) or standard care (n = 200) at one of three drop-in centers serving homeless youth in the Los Angeles area. We will evaluate intervention effects on primary outcomes of AOD use and sexual risk behavior, as well as secondary outcomes of health-related quality of life and social stability, over a 12-month period.

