Recruitment occurs in a series of 16-week cycles, with the three drop-in center sites alternating across cycles in serving as the intervention site or control site (see Fig. 1). Recruitment is done by advertising the study at the drop-in centers, and through soliciting volunteers during recruitment visits. Individuals sign up on a sign-in sheet each day to participate in the study. Depending upon the number who sign up, they are randomly selected from the pool of interested individuals and screened for eligibility. Eligible participants provide written consent and complete a baseline scannable self-report survey, which takes approximately 30 min, and is completed in the presence of a staff member who can provide assistance if needed. Participants in both conditions are recruited during the first 8 weeks of each cycle, until our target enrollment number for that cycle is reached, which leaves the remainder of the cycle as a “wash out” period to reduce the likelihood of contamination across conditions. The four-session AWARE program is delivered four times during each 16-week cycle, allowing intervention participants multiple opportunities to complete all sessions. Figure 2 depicts participant flow through the study, and Fig. 3 contains a SPIRIT (Standard Protocol Items: Recommendations for Interventional Trials) flow diagram of the RCT schedule of enrollment, interventions, and assessments.

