We initially considered a design in which individuals would be randomly assigned to condition within agency. However, we decided against this design given concerns on the part of the research team and drop-in center staff about implementation challenges (e.g., clients perceiving that they were being refused services that other clients were getting) and the strong potential for contamination across conditions. A group-randomized design was a much better option for this evaluation in that it addressed these concerns. We are maximizing the comparability of the intervention and control groups by having each drop-in center serve as both intervention and control site on an alternating basis, as well as using the same procedures at each drop-in center to identify and recruit participants for the study. In addition, once data are collected, we will conduct preliminary analyses to determine whether the intervention and control groups differ on baseline characteristics. This step is necessary despite randomization as randomization is not occurring at the individual level. In the pilot evaluation, which used the same procedure, there were no significant baseline group differences on demographic characteristics. However, any observed differences will be controlled for in all analyses testing intervention effects with the addition of model covariates. If we observe considerable differences in the intervention and control groups that cannot be adequately accounted for with the addition of model covariates, we will develop analytic weights using propensity methods to balance the groups. We will also control for any within-agency effects by including agency as a fixed effect (dummy coded) within the models.

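### Whether to adjust for baseline covariates is optional in one section and mandatory in another, and apart from agency the choice rests on a baseline significance test

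*Protocol article*

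**What the plan says.** Two sections of the protocol article describe how covariates are chosen.

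- **Analytic plan (the first section of that name, before the outcome sections).** Preliminary analyses will "determine whether the intervention and control groups differ on baseline characteristics (t-tests and Chi square tests"). Differences at p < "0.20 may be subsequently controlled for in analyses testing intervention effects".
- **Limitations and alternative methods considered.** The same preliminary comparison is described, with a reason: "This step is necessary despite randomization as randomization is not occurring at the individual level". The text goes on to say that "any observed differences will be controlled for in all analyses testing intervention effects with the addition of model covariates". If considerable differences remain that covariates cannot adequately handle, "we will develop analytic weights using propensity methods to balance the groups". Agency effects are handled by "including agency as a fixed effect (dummy coded) within the models".

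Neither section lists the baseline variables to be tested. Neither names any covariate, other than agency, that enters the models whatever the test shows. The second Analytic plan section sets out tests at 3, 6 and 12 months and longitudinal analyses of change. It does not say whether the time-point tests adjust for the baseline value of the outcome.

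**The concern.** There are two separate problems.

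1. **The instructions differ.** One section permits adjustment and the other requires it in all analyses. An analyst who finds a variable at p = 0.15 may leave it out under the first and must include it under the second. A variable at p = 0.30 is outside the first rule and arguably inside the second.
2. **The selection criterion is a poor one under either wording.** A baseline p-value says how far the arms differ on a variable, not how strongly that variable predicts the outcome. A strong predictor that happens to balance is left out, and an irrelevant variable that happens to differ is flagged. The t-tests and chi-square tests also take participants as independent, although condition is assigned by site and cycle.

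At stake are precision that costs nothing to obtain, and a primary model that is known only after the data have been examined, across many outcomes and three time points.

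**Working it through.** The article states no power or alpha calculation that bears on this point, so there is no figure to reproduce. What follows sizes the consequence.

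**Inputs from the article.** Participants "will receive the AWARE risk reduction program (n = 200) or standard care (n = 200"), so 200 per arm. The screen is p < 0.20. There are three sites, "with the three drop-in center sites alternating across cycles in serving as the intervention site or control site".

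**Inputs assumed, because the article gives none.** d = 0.25; two-sided α = 0.05; one baseline predictor with correlation ρ to the outcome; independent participants for the power figures. For the flag rate, six cycles and a site-by-cycle ICC of 0.02 to 0.05.

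**Step 1: no adjustment.** The expected z is d·√(n/2) = 0.25 × √100 = 2.5. Power is Φ(2.5 − 1.96) = Φ(0.54) ≈ 0.705.

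**Step 2: fixed adjustment.** The expected z becomes 2.5/√(1 − ρ²).
- ρ = 0.3: 2.5/0.954 = 2.62, power Φ(0.66) ≈ 0.746
- ρ = 0.5: 2.5/0.866 = 2.89, power Φ(0.93) ≈ 0.823
- ρ = 0.6: 2.5/0.8 = 3.125, power Φ(1.165) ≈ 0.878

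**Step 3: adjust only if the baseline test gives p < 0.20.** With no systematic imbalance, the predictor is flagged 20% of the time and left out 80% of the time. Rejection probability = 0.20 × (adjusted rejection rate) + P(not flagged and unadjusted test rejects). The last term comes from a bivariate normal with correlation ρ between the baseline and outcome z-statistics, restricted to |z baseline| < 1.28. At ρ = 0.5:
- power: 0.20 × 0.823 + 0.576 = 0.740
- type I error: 0.20 × 0.05 + 0.027 = 0.037

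**Step 4: simulated results for the same setting.**

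| ρ | Power, screened | Power, fixed | Type I error, screened |
|---|---|---|---|
| 0.3 | 71% | 74% | 4.5% |
| 0.5 | 73% | 82% | 3.9% |
| 0.6 | 76% | 87% | 3.3% |

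These agree with steps 2 and 3 to within about one percentage point.

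**Step 5: optional adjustment used opportunistically.** Suppose that, when the variable is flagged, the smaller of the adjusted and unadjusted p-values is taken. In 20,000 replicates the type I error is 5.3%, 5.8% and 5.3% at ρ = 0.3, 0.5 and 0.7, against 5.0%, 5.4% and 4.9% for the unadjusted test in the same runs. The excess is at most about 0.5 points for one covariate and one outcome.

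**Step 6: flag rate when clustering is ignored.** With 3 sites × 6 cycles = 18 cells, there are 400/18 ≈ 22.2 participants per cell. The design effect is 1 + 21.2 × ICC, which is 1.42 at ICC 0.02 and 2.06 at 0.05. The flag rate is 2·(1 − Φ(1.28/√DE)), or about 28% and 37% instead of 20%. Simulation gave 29% and 37%.

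**The case against.** The strongest reply has four parts.

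- **The conflict is narrower than it looks.** Both sections describe the same preliminary comparison, and the first uses the phrase observed differences for what passes p < 0.20. On that reading the thresholds agree and only *may* against *will* conflicts. Propensity weighting is a sequential fallback, so the text does not support a reading of three rival rules. This stands. The mismatch in force remains.
- **Imbalance need not be chance.** Sites alternate and individuals are not randomised, so a balance check guards against bias, and the article says so. A reader might infer that the check should be dropped, and the design does not support that. It does not rescue selection by p-value, though: a possible systematic imbalance is a reason to adjust for prognostic variables whatever the test shows.
- **Some of this is already handled.** Agency is fixed in advance. The longitudinal analyses of change probably use baseline values, which would shrink the power loss there. A fuller covariate list could sit in an analysis plan that is not shown. All fair, but the article states a selection rule, and such a plan could not follow both wordings.
- **The size rests on assumptions.** The power figures ignore clustering and the flag rates assume it, so they do not describe one trial. At ρ = 0.3 the gain is only 2 to 3 points. This stands too.

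**Conclusion.** The point holds in limited form. The two sections disagree on whether adjustment is optional, and on the threshold unless observed differences is read as those at p < 0.20. Apart from agency, adjustment is driven by a test of imbalance that ignores site-by-cycle clustering.

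For a single predictor with ρ between 0.3 and 0.6, the cost is roughly 3 to 11 points of power at d = 0.25, and less wherever baseline values already enter the model. The values of d, ρ, ICC and the number of cycles are all assumed, and the power figures take participants as independent.

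Two stronger readings are not supported. A reader might infer an inflated type I error, but strict screening makes the test conservative, and discretion over one covariate and one outcome adds at most about half a point. Discretion across several covariates, outcomes and the weighting option was not quantified. A reader might also infer that every flagged variable will enter the model, but the section that sets the p < 0.20 screen only permits this.

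**What to change.** Replace both wordings with one rule, stated identically in the two sections:

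- Every outcome model, including the separate tests at 3, 6 and 12 months, adjusts for the baseline value of that outcome and for agency.
- Add a short list of prognostic covariates that are already collected, named before outcome data are seen. Which ones is for the investigators to justify.
- Keep the baseline balance check and the propensity-weighting fallback, since individuals are not randomised. Judge balance by standardised differences rather than p-values.
- Report any further imbalance-driven adjustment or weighting as additional to the prespecified primary model.

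The cost is a change of wording and a decision on the list, with no new data collection.

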### Main outcomes of the intervention

The main outcome variables are AOD use and sexual risk behavior at 3-, 6-, and 12-month follow-up. Using items based on the Monitoring the Future survey [82], we will assess the number of days, in the past 30 days, participants engaged in the use of various substances, including alcohol use, heavy alcohol use, cannabis use, non-medical prescription drug use, and use of several types of illicit drugs (e.g., heroin, methamphetamine, hallucinogens). Information is also collected on the quantity of alcohol use (drinks per day) and marijuana use (times per day) on the days these substances are used. We are administering the Global Appraisal of Individual Needs–Short Screener (GAIN-SS) [83] to explore whether intervention effects on AOD outcomes might be weaker for those with a high probability of a past year substance use disorder (scores of 3 or greater), compared to those with a low-moderate probability of a disorder. In addition, we assess the importance of cutting down or stopping their alcohol, marijuana, and other drug use (or, if they do not currently use, the importance of remaining a non-user) with separate motivation to change rulers for each type of substance (0 = *not at all important* to 10 = *extremely important*) [84]. We are assessing sexual risk behavior using both past 90 day and past 30 day timeframes, with the main outcome being the proportion of unprotected sexual events. In addition, we are assessing condom use self-efficacy using the Self-Efficacy Instrument for Protective Sexual Behaviors [85].

### Secondary outcomes of the intervention

Secondary outcome variables for these analyses will include measures of health-related quality of life and stability. Mental functioning will be as assessed with the eight-item Patient Health Questionnaire (PHQ-8) [87] for symptoms of depression in the past 2 weeks (e.g., feeling down, depressed, or hopeless; 0 = *not at all* to 4 = *nearly every day*). Physical functioning will be assessed with items from the Physical Health Questionnaire [88], which focus on a variety of physical symptoms (e.g., difficulty sleeping, headache; 1 = *not bothered at all* to 3 = *bothered a lot*), as well as the widely used general health status item from the SF-12 (1 = *poor* to 5 = *excellent*) [89]. Social functioning will be assessed in terms of friend support in the past 30 days, using items from the PROMIS Pediatrics Peer Relationship Scale (e.g., I was able to count on my friends; 1 = *never* to 5 = *almost always*) [90], and overall satisfaction with friends (single item: 1 = *not at all satisfied* to 5 = *extremely satisfied*). Education variables include current educational attainment (1 = *no high school degree* to 5 = *college graduate*) and educational aspirations (1 = *I do not intend to receive a high school diploma or GED* to 5 = *graduate school degree*). Employment variables include current employment status, number of different paid jobs in the past 3 months, and longest time spent in any one job in the past 3 months [91]. Economic stability is assessed in terms of income in the past 30 days from various sources (e.g., job, relatives or friends, government assistance, street economy) [92], and items asking how much of a problem it was in the past 3 months to get clothes, medical care/treatment, a place to clean up, a clean and safe place to sleep, and enough to eat, (0 = *none* to 4 = *a great deal*) [93, 94]. Housing stability is assessed with items adapted from Tsemberis et al. (2007) [95], asking how often they had spent the night in various locations in the past 3 months (e.g., their own house, apartment or room; someone else’s apartment or house; emergency shelter; transitional housing program; outdoors, the street, or a park; car or other private vehicle; abandoned building; hotel/motel; 0 = *never* to 7 = *everyday*).

### Analytic plan

We will compare the intervention and control groups on each of the primary and secondary outcomes with a multilevel modeling approach using SAS PROC MIXED for continuous outcomes (e.g., past month quantity-frequency of alcohol use; proportion of protected sex acts; past month income) and PROC GLIMMIX for categorical or count outcomes with overdispersion and/or zero-inflation accounted for as needed in the modeling approach (e.g., any past month heavy drinking; number of sex partners; number of jobs in past 3 months) using restricted maximum likelihood estimation. Outcomes will be tested at each time point (3-, 6-, and 12-months) and longitudinal analyses will be used to test for differences in change over the 12-month period. Although testing at each time point provides estimates of the intervention effect at that time, the longitudinal analysis will capture patterns of change over time, that is, whether the average change on outcomes within each group produce parallel lines over time vs. lines with different slopes vs. non-linear patterns. We will explore dose–response relationships given that participants voluntarily choose to attend 1 to 4 program sessions. Although we consider any attendance as receiving the intervention, attending more sessions may be associated with better outcomes [86]. In addition, we will conduct an analysis to explore whether observed program effects differ by gender or substance use severity (defined by a score of 3 or higher on the GAIN-SS) [83] by estimating separate models for each group and/or by including an interaction term in the models.

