## Substance use is common among young people experiencing homelessness as well, and is often associated with sexual risk behavior

High rates of AOD use [3, 17–21], including injection drug use [22, 23], are consistently found in studies of youth experiencing homelessness. For example, in a survey of 419 homeless youth in Los Angeles County, past month AOD use was reported by 68% for alcohol, 66% for cannabis, 15–16% for methamphetamine and ecstasy, and 9% for injection drugs [19, 24]. An estimated 60%–70% of homeless youth meet lifetime criteria for a substance use disorder [25–28]. Thus, it is not surprising that many homeless youth engage in sex while high or intoxicated [16, 29]. AOD use is also a risk factor for HIV/STD transmission through its association with high-risk sexual behavior such as unprotected sex, sex with a partner who injects drugs or is HIV-positive, and trading sex [16, 30–33].

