## Methods/design

### Participants

The intervention is targeted towards young adults experiencing homelessness. Thus, eligibility criteria include: 1. being between the ages of 18 and 25; 2. seeking services (e.g., food, clothing) at one of the participating drop-in centers serving young people experiencing homelessness in Los Angeles County; 3. no cognitive impairment observed during the screening process; 4. planning to be in the study area for the next month; and 5. English speaking. We are focusing specifically on 18–25 year olds in this study for three reasons: (a) the vast majority (85%) of the unaccompanied homeless youth population is in this age range; (b) a wider age range among participants may adversely affect group cohesion and dynamics in this group-based program; and (c) important developmental differences between adolescents (12–17) and young adults would require tailoring of the program curriculum and conducting separate groups, which is beyond the scope of this study. AWARE can be used as both prevention and intervention; as such there are no eligibility criteria based on substance use severity. Although there is less compelling evidence that brief MI is effective with people who have severe substance use disorders, we do not want to withhold a potentially beneficial treatment from anyone who is interested in the program. We also want to provide our program to those who are interested even if they do not fit a threshold for heavy AOD use. Fortunately, our pilot results suggest that the AWARE program is appropriate and beneficial for homeless young adults in general, and not just those who are at relatively low risk (based on GAIN-SS scores in the case of substance use outcomes, and number of sex partners in the case of sexual behavior outcomes) [1]. We plan to enroll 400 participants at baseline, who are expected to represent the demographics of the broader population of 18–25 year olds experiencing homelessness in Los Angeles County. All study materials and procedures will be approved by RAND’s Human Subjects Protection Committee and a Certificate of Confidentiality from the National Institutes of Health will protect data from subpoena.

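### Restricted maximum likelihood is stated for PROC GLIMMIX as well as PROC MIXED; in the longitudinal binary models this means pseudo-likelihood, which would shrink person-specific odds ratios towards 1

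*Protocol article*

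**What the plan says.** In the protocol article, the *Analytic plan* section that follows the secondary outcomes describes group comparisons "with a multilevel modeling approach using SAS PROC MIXED for continuous outcomes" and "PROC GLIMMIX for categorical or count outcomes with overdispersion and/or zero-inflation accounted for as needed in the modeling approach". The examples for GLIMMIX are "any past month heavy drinking; number of sex partners; number of jobs in past 3 months", so one binary variable and two counts. The same sentence ends "using restricted maximum likelihood estimation", with nothing to confine that estimator to PROC MIXED.

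Two kinds of analysis follow, the second spanning the full year: "Outcomes will be tested at each time point (3-, 6-, and 12-months) and longitudinal analyses will be used to test for differences in change". *Limitations and alternative methods considered* adds that agency effects are handled by "including agency as a fixed effect (dummy coded) within the models". On size, the *Participants* section says: "We plan to enroll 400 participants at baseline". The article gives no random-effect structure, person-level variance, target odds ratio or likelihood approximation.

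**The concern.** Restricted maximum likelihood belongs to the linear mixed model. It suits the outcomes sent to PROC MIXED. For a logistic or count mixed model, the nearest equivalent repeatedly linearises the data and applies a restricted likelihood to the working response (restricted pseudo-likelihood). The approximation is poor when each cluster holds only a few binary records and those records are strongly correlated.

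That situation can arise here. Agency is fixed, so the natural random effect in a longitudinal model is the person, who contributes three follow-up records, or four if baseline is treated as a response. Heavy drinking is listed under *Main outcomes of the intervention*, and its past-month indicator is the plan's own GLIMMIX example. At stake is the size of the reported longitudinal odds ratio, which readers and later syntheses would use, and the reported between-person variance.

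**Working it through.** The article states no power, effect size or variance, so there is no figure of its own to reproduce. The check simulates the stated estimator against full maximum likelihood.

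**Inputs from the article:** 400 people, 200 per condition; three follow-ups; agency as a fixed effect; a binary outcome in a multilevel longitudinal model.

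**Assumptions, not in the article:** a person random intercept; its variance on the logit scale from 0.5 to 8; a true person-specific odds ratio (OR) of 0.60 (log OR −0.511); intercept 0 (about 50% base rate) or −2 (low rate); 15% of visits missing.

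**Model:** logit P(y = 1) = intercept + visit + agency + β × arm + u, with u normal with mean 0 and variance σ². Each of 60 data sets per setting was fitted (a) by restricted pseudo-likelihood and (b) by maximum likelihood with 25-point Gauss–Hermite quadrature. Shrinkage = 1 − (pseudo-likelihood log OR ÷ quadrature log OR), paired within data sets.

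| σ² | paired ratio (50% rate / low rate) | shrinkage | pseudo-likelihood σ² |
|---|---|---|---|
| 0.5 | 0.919 / 0.955 | 8% / 4.5% | 0.28 / 0.27 |
| 1 | 0.851 / 0.872 | 15% / 13% | 0.53 / 0.55 |
| 2 | 0.771 / 0.795 | 23% / 20.5% | 0.89 / 0.82 |
| 4 | 0.681 / 0.669 | 32% / 33% | 1.42 / 1.34 |
| 8 | 0.570 / 0.569 | 43% / 43% | 2.03 / 1.94 |

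At σ² = 4 the true OR of 0.60 was reported on average as 0.71–0.73. With four records per person the ratio was 0.86 at σ² = 1 and 0.71 at σ² = 4, so including baseline does not remove the problem.

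**Is quadrature a sound comparator?** Its mean ORs lay between 0.55 and 0.62. The furthest, 0.55 (σ² = 1, low rate), is (0.171 × 0.511) ÷ (0.207/√60) = 3.3 Monte Carlo standard errors from the truth. A fresh run of that setting with 200 data sets gave a quadrature log OR of 1.02 times the truth (standard error 0.03) and a paired ratio of 0.89, so the excess was chance.

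**A separate simulation**, with true log OR −0.80 and 100 data sets per setting, gave pseudo-likelihood means of −0.66, −0.57 and −0.49 at σ² = 2, 4 and 6. Against the truth that is 1 − 0.66/0.80 ≈ 18%, 1 − 0.57/0.80 ≈ 29% and 1 − 0.49/0.80 ≈ 39%, in line with the table.

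**Effect on the test.** The mean estimate divided by its empirical standard deviation at σ² = 4 was 1.68 (pseudo-likelihood) against 1.70 (quadrature) at the 50% rate, and 1.81 against 1.79 at the low rate. Estimate and standard deviation shrink together.

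**Counts.** With Poisson data, a true rate ratio of 0.70 and 150 data sets per setting, the pseudo-likelihood log rate ratio was 0.97–0.98 of the truth at σ² = 0.5 and 0.86–0.94 at σ² = 1 (Monte Carlo standard error about 0.02–0.03).

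**The case against.** Much can be said for the plan.

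- **Few outcomes are exposed.** *Main outcomes of the intervention* defines substance use mainly as days of use out of the last 30, and the main sexual outcome as a proportion. Alcohol quantity-frequency and the proportion of protected acts go to PROC MIXED, where the estimator is right. A reader might infer that an any-use indicator for every drug is a main outcome with a biased odds ratio. The article states no such analyses, and its one binary GLIMMIX example is an illustration. This stands.
- **Tests at single time points.** With one record per person and agency fixed, this mechanism does not reach them. This stands.
- **The comparison of groups.** A reader might infer that shrinkage costs power. The ratios of estimate to standard deviation show that it hardly does. This stands.
- **The estimand.** The article does not commit to a person-specific odds ratio. By the usual approximation, the population-averaged log OR is the person-specific one divided by √(1 + 0.346σ²). At σ² = 4 that is −0.511/1.544 = −0.331, an OR of 0.72, close to what pseudo-likelihood returned. But pseudo-likelihood targets neither quantity by design, so this is a reason to name the target and not a defence of the estimator.
- **Zero-inflation.** It is tempting to say that this step cannot be run in GLIMMIX, and to point to the survey in the Background with past-month use of "15–16% for methamphetamine and ecstasy, and 9% for injection drugs" as implying 84–91% zeros. The article names no zero-inflated distribution, and a two-part analysis would satisfy its wording. What the software offers cannot be checked from the document. Many zeros alone are not zero-inflation, and injection drug use is not named among the main outcome measures. This is not a demonstrated error.
- **Model choice.** A reader might also infer that distributions or time trends will be compared by restricted or pseudo-likelihoods. The article never says so; a Pearson dispersion statistic and Wald or F tests would serve.
- **Condensed article.** A fuller plan may give the GLIMMIX options. That would excuse silence, but here an estimator is stated.

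**Conclusion.** The point holds in a limited form. As written, the estimator for longitudinal binary outcomes in GLIMMIX amounts to restricted pseudo-likelihood. With a person random effect and three records each, it would understate the person-specific log odds ratio by about 4–15% at a person variance of 0.5–1, 20–33% at 2–4 and 43% at 8, and it would understate that variance too (about 1.4 for a true 4). These figures rest on an assumed random-intercept model and assumed variances; if the random effect sits at another level, they do not apply. The harm is to the size of the reported effect. It does not extend to the group test or to the single-visit analyses, and it is smaller for counts.

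**What to change.** Confine restricted maximum likelihood to PROC MIXED. For longitudinal binary and count mixed models in PROC GLIMMIX, specify maximum likelihood by adaptive quadrature or Laplace (METHOD=QUAD or METHOD=LAPLACE), with the negative binomial for overdispersed counts, and state the random-effect structure. Alternatively, declare a population-averaged odds ratio as the target and fit a marginal model, accepting that it will lie closer to 1 than the person-specific one. If excess zeros must be modelled, name a two-part analysis: any use, then days among users.

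The cost is a method option, a sentence or two of text and longer run time. No design or data-collection change is needed.
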